## Abstract

**Background:**

Neoadjuvant chemoradiotherapy (CRT) followed by total mesorectal excision (TME) has been a standard treatment option for locally advanced rectal cancer with improved local control. However, systemic recurrence despite neoadjuvant CRT remained unchanged. The only significant prognostic factor proven to be important was pathologic complete response (pCR) after neoadjuvant CRT. Several efforts have been tried to improve survival of patients who treated with neoadjuvant CRT and to achieve more pCR including adding cytotoxic chemotherapeutic agents, chronologic modification of chemotherapy schedule or adding chemotherapy during the perioperative period. Consolidation chemotherapy is adding several cycles of chemotherapy between neoadjuvant CRT and TME. It could increase pCR rate, subsequently could show better oncologic outcomes.

**Methods:**

Patients with advanced mid or low rectal cancer who received neoadjuvant CRT will be included after screening. They will be randomized and assigned to undergo TME followed by 8 cycles of adjuvant chemotherapy (control arm) or receive 3 cycles of consolidation chemotherapy before TME, and receive 5 cycles of adjuvant chemotherapy (experimental arm). The primary endpoints are pCR and 3-year disease-free survival (DFS), and the secondary endpoints are radiotherapy-related complications, R0 resection rate, tumor response rate, surgery-related morbidity, and peripheral neuropathy at 3 year after the surgery. The authors hypothesize that the experimental arm would show a 15% improvement in pCR (15 to 30%) and in 3-year DFS (65 to 80%), compared with the control arm. The accrual period is 2 years and the follow-up period is 3 years. Based on the superiority design, one-sided log-rank test with α-error of 0.025 and a power of 80% was conducted. Allowing for a drop-out rate of 10%, 358 patients (179 per arm) will need to be recruited. Patients will be followed up at every 3 months for 2 years and then every 6 months for 3 years after the last patient has been randomized.

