### Sample size calculation and randomization

Based on literatures, pCR rates and 3-year DFS after CRT for rectal cancer were known to be 10 to 28% and 50-65%, respectively [2, 6, 8–13]. Thus we hypothesize that the experimental arm would show a 15% improvement in pCR and in 3-year DFS, compared with the control arm (15 to 30% and 65 to 80%, respectively). The accrual period is 2 years and the follow-up period is 3 years. Based on the superiority design, one-sided proportion test and log-rank test with α-error of 0.025 and a power of 90% was conducted for both primary endpoints: pCR and 3-year DFS. The pCR of each group was considered to be 15 and 30%, and the 3-year DFS of each group was considered to be 65 and 80% assuming that accrual time was 2 years and follow up time was 3 years. Allowing neoadjuvant CRT for a drop-out rate of 10%, 358 patients (179 per arm) for pCR and 316 patients (158 per arm) for 3-year DFS will need to be recruited. Therefore a total of 358 participants (among 358 and 316) are needed. This study of 358 participants had at least 81% power (90% each = 0.9, so 0.9 × 0.9 = 0.81) to simultaneously detect a difference of pCR and 3-year DFS of two groups. Randomization will be performed in a 1:1 ratio by computer-generated random numbers, with the use of stratified permuted 4 blocks. It will stratified according to age (< 70 vs. ≥70), clinical T stage (T1/2 or T3), and clinical N stage (N0 or N1/2). Among 8 strata, 2 strata will not be used because clinical T1/2 N0 (age < 70 and ≥ 70) are not indicated for neoadjuvant CRT.

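### The Abstract ties 358 patients to a log-rank test at 80% power, but 358 is the pCR proportion-test size at 90% power

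*Protocol article*

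**What the plan says.** The Methods paragraph of the Abstract names one test and one power: a "one-sided log-rank test with α-error of 0.025 and a power of 80% was conducted". The next sentence gives 358 patients, 179 per arm, after allowing for 10% drop-out.

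The section on sample size calculation and randomization describes two calculations, a one-sided proportion test and a log-rank test, "with α-error of 0.025 and a power of 90% was conducted for both primary endpoints". It assigns a size to each endpoint: "358 patients (179 per arm) for pCR and 316 patients (158 per arm) for 3-year DFS". It takes the larger and states at least 81% power (0.9 × 0.9) to detect both differences together.

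The two places agree on the one-sided α of 0.025, the effect sizes (pCR 15 vs 30%, 3-year DFS 65 vs 80%), accrual, follow-up, drop-out rate and the total of 358. They disagree on the power and on which test produces the 358.

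**The concern.** Both statements are current text and cannot both be right. One sets the power at 80%, the other at 90% per endpoint; one attributes 358 to the log-rank test for DFS, the other to the proportion test for pCR.

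The planned power and the endpoint that drives the size are what a reader uses to weigh a null result. In a trial with two primary endpoints, someone relying on the Abstract would take the type II error on DFS to be 20%, would see no power for pCR at all, and could not re-derive 358 from the inputs given.

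**Working it through.** **Inputs.** From the sample size section: one-sided α 0.025; pCR 15 vs 30%; 3-year DFS 65 vs 80%; 1:1 allocation; 2 years' accrual and 3 years' follow-up; drop-out 10%. Normal quantiles: 1.960 for α, 1.2816 for 90% power, 0.8416 for 80% power. Assumptions made here: exponential DFS, uniform accrual, and drop-out applied as n/0.9.

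**Step 1. Reproduce 358 from the sample size section (pCR, 90%).** Pooled-variance formula without continuity correction:

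n per arm = [1.960·√(2·0.225·0.775) + 1.2816·√(0.15·0.85 + 0.30·0.70)]² / 0.15²

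= [1.1575 + 0.7445]² / 0.0225 = 160.8, so 161.

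161/0.9 = 178.9, so 179 per arm and **358 in total**. Exact match.

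**Step 2. Reproduce 316 from the sample size section (DFS, 90%).**

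- Hazard ratio = ln 0.80 / ln 0.65 = 0.518.
- Schoenfeld events = 4·(1.960 + 1.2816)² / (ln 0.518)² = 97.1, so 98.
- Yearly hazards: −ln 0.65/3 = 0.1436 and −ln 0.80/3 = 0.0744.
- Event probability with 2-year accrual and 3 further years, 1 − (e^(−3λ) − e^(−5λ))/(2λ): 0.435 and 0.257, mean 0.346.
- 98/0.346/2 gives 142 per arm; 142/0.9 = 157.8, so 158 per arm and **316 in total**. Exact match.

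**Step 3. The Abstract's combination (log-rank, 80%).**

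- Schoenfeld events = 4·(1.960 + 0.8416)² / (ln 0.518)² = 72.6, so 73.
- 73/0.346/2 gives 106 per arm; 106/0.9 = 117.8, so 118 per arm and **236 in total**. Carrying 72.6 events unrounded gives 117 per arm, 234 in total.

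**Step 4. Could another formula or reading of the follow-up give 358?** Totals after drop-out, log-rank at 80%:

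| Follow-up reading | Schoenfeld | Freedman | Lachin-Foulkes |
|---|---|---|---|
| 2 years' accrual + 3 years | 236 | 252 | 250 |
| Exactly 3 years per patient | 296 | 316 | 314 |
| 3 years total study time | 424 | 452 | 450 |

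None is within 3% of 358. The last row conflicts with the Abstract, which counts follow-up from the last randomization.

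**Step 5. Does changing only the test rescue 80%?** The pCR proportion test at 80% needs 120.5, so 121 per arm; 121/0.9 gives 135 per arm, 270 in total (298 with continuity correction). It does not.

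**Step 6. Power that the trial has.** With 161 evaluable per arm, power is 90.0% for pCR and about 93% for the DFS log-rank test (Schoenfeld, 2 + 3 years). With exactly 3 years per patient, DFS power is about 87%.

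**The case against.** The best defence is that the 80% is a loose rendering of the 81% joint power in the sample size section. That may well be its origin. But the Abstract never calls it joint; it attaches it to a single log-rank test. Joint power is the chance of detecting both effects, which is not the power of the DFS test.

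A second defence is that an abstract condenses. Leaving out the proportion test would be condensing. Naming a test and a power that do not yield the number in the next sentence is a misstatement.

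Two points on the other side stand:

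- How far the Abstract's combination falls from 358 depends on the formula and on how follow-up is read, so 236 should be quoted with the 2 + 3-year assumption. The exact match at 316 is likewise specific to Schoenfeld's formula at 90%. Freedman's at 80% with exactly 3 years per patient also happens to give 316, but that is neither the power nor the accrual pattern stated beside the figure. Neither point touches the 358.
- The consequence is confined to reporting. The full calculation is in the article, the target is the same in both places, and under the 2 + 3-year assumption the Abstract understates the power rather than overstating it.

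**Conclusion.** The concern holds. The sample size section reproduces to the patient (358 for pCR, 316 for DFS, both at 90%). The Abstract's attribution does not reproduce under any variant tried; with 2 + 3 years it would call for about 236 patients (234 to 252 by formula and rounding), roughly two thirds of 358.

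The size of the trial is not in question. What is wrong is the stated test and power: the implied 20% miss rate on DFS compares with about 7% at 161 evaluable per arm. That 7% rests on exponential DFS, the planned effect, 2 + 3 years and 10% drop-out; with exactly 3 years per patient it is about 13%. This should be corrected, but it does not affect the conduct of the trial.

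**What to change.** Replace the Abstract sentence with one that agrees with the sample size section, for example: *With a one-sided α of 0.025 and 90% power for each primary endpoint, and allowing for 10% drop-out, 179 patients per arm are needed for pCR (proportion test) and 158 per arm for 3-year DFS (log-rank test); the larger, 358 in total, will be recruited, giving at least 81% power to detect both differences.*

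The 81% is carried over as the sample size section states it, and it presumes that DFS is tested by log-rank. The Objective section defines 3-year DFS as a proportion; if that definition is kept for the test, the joint figure needs recalculating.

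The cost is one sentence, plus any other text that repeats it. The recruitment target and the analysis do not change.

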**Discussion:**

KONCLUDE trial aims to investigate whether consolidation chemotherapy shows better pCR and 3-year DFS than adjuvant chemotherapy alone for the patients who received neoadjuvant CRT for locally advanced rectal cancer. This trial is expected to provide evidence to support clear treatment guidelines for patients with locally advanced rectal cancer.

**Trial registration:**

Clinicaltrials.gov NCT02843191 (First posted on July 25, 2016).

## Background

Neoadjuvant chemoradiotherapy (CRT) followed by total mesorectal excision (TME) is the standard treatment for local advanced mid- or low rectal cancer [1, 2]. Reduction of local recurrence has been proven after introduction of TME for rectal cancer [3]. Additionally, chemotherapy and/or radiotherapy have shown the roles to improve oncologic outcomes by controlling local recurrence. Preoperative chemoradiotherapy showed better outcomes compared with postoperative chemoradiotherapy or preoperative radiotherapy alone [4–8].

However, failure of systemic controls including liver, lung, peritoneum, or bone still remained even after CRT followed by TME [1, 4, 5]. Many efforts have been made to control micrometastatic disease and to prevent distant and local recurrence. So far, no reliable molecular or pathologic biomarkers to foster pathologic complete response (pCR), which means complete regression of the tumor after radiotherapy and/or chemotherapy, was identified. Meanwhile, patients who showed pCR have been reported with lower recurrence and better survival [9, 10]. Therefore, many trials have been performed to increase pCR rates by changing perioperative treatment strategies.

Prolongation of the interval between CRT and TME has shown to increase pCR rates [11]. The interval has prolonged recently from 6 to 8 weeks up to 12 weeks, and several authors reported that extending the interval showed better pCR rates without increasing morbidity. [12–15] Another tries to achieve more pCR were adding platinum analogue (i.e. oxaliplatin) or vascular endothelial growth factor antagonist (i.e. bevacizumab) preoperatively and/or postoperatively based on 5-FU [16–18]. Unfortunately most of them failed to show higher pCR rates but increased acute toxicity [19, 20]. Recent trials reported that changing sequence of chemotherapy cycles as well as chemotherapeutic agents would attain better pCR rates, and new trials are launching. The examples are induction chemotherapy, consolidation chemotherapy, and sandwich regimen (prior to, concurrently with, and following radiation therapy) [21–26]. Sandwich regimen with capecitabine and oxaliplatin accompanied by 25 Gy of radiotherapy resulted in 42.2% of pCR rates, and even 10% of patients needed no surgery because the patients had achieved clinical complete response [22]. Garcia-Aguilar et al. reported that pCR rates were significantly increased in the patients who received various cycles of consolidation chemotherapy of FOLFOX regimen without significantly increased toxicity [21]. Then they showed that additional consolidation chemotherapy resulted in higher pCR rates in their multicenter, phase 2 trial [23]. However, it is not sufficient to conclude that consolidation chemotherapy is the only affecting factor to pCR due to several limitations. The interval and duration of consolidation chemotherapy were variable from 6 to 20 weeks. Moreover, adjuvant chemotherapy after TME followed by CRT was not standardized, and the total doses or cycles of chemotherapy was not consistent equally. Therefore, well-designed randomized controlled trials to assess the effect of consolidation chemotherapy alone after neoadjuvant chemoradiotherapy for locally advanced mid or low rectal cancer is required.

## Methods/design

### Study design

This trial is a phase 3 trial investigating the efficacy of 3 cycles of consolidation chemotherapy between neoadjuvant CRT and TME for locally advanced rectal cancer. To prove the effects of consolidation chemotherapy, we will administer the equal schedules of chemotherapy (8 cycles of mFOLFOX6 chemotherapy) in both groups.

Patient selection criteria are as follows:Inclusion CriteriaAn adult aged 20-75 years oldHistologically confirmed adenocarcinoma of mid or low rectum (i.e. the lower margin of tumor located below the peritoneal reflection or within 12 cm from the anal verge by digital rectal examination, rigid proctosigmoidoscopy or MRI measurement from sagittal T2 weighted image)Locally advanced rectal cancer confirmed by magnetic resonance image (MRI): Clinical stage T1-3N1or2 or clinical stage cT3N0 (or depth of perirectal invasion by tumor > 5 mm on MRI), or suspicious of circumferential invasion on MRI (or circumferential margin < 1 mm)ECOG performance status of 0-2ASA score of ≤ 3An informed consent form has been signed by the patient.Exclusion CriteriaUpper rectal cancer (i.e. the lower margin of tumor located above the peritoneal reflection)Clinical stage T1or2N0 on MRIClinical stage T4Nany on MRI (T4 lesion would be complicated to manage)Distant metastasis diagnosed by imaging diagnosis or histologyThe patient received chemotherapy or radiotherapy during the past 6 monthsThe patient received any therapy for colorectal cancer or another malignancy during the past 5 yearsThe patient has severe underlying diseases or poor condition to receive chemotherapy or radiotherapyPregnant of breastfeeding womenThe patient who participate in another clinical trial, or receives any drug for the trialUncontrolled peripheral neuropathy (> Grade 2)Any unhealed wound, fracture, peptic ulcer, or intraabdominal abscessActive gastrointestinal bleedingPatients with an active infection, which needs antibiotic therapy, during the randomization period

All the patients who received CRT (50.4 Gy radiation with capecitabine 825 mg/m^2^ twice daily for 28 days) will be randomized in a 1:1 ratio into one of the following arms after screening: conventional chemotherapy group (control arm: Arm 1) or consolidation chemotherapy group (experimental arm: Arm 2) (Fig. 1). Stratification factors are age (< 70 or ≥ 70), clinical T stage (T1/2 or T3), and clinical N stage (N0 or N1/2). All eligible patients will be enrolled from approval of institutional review board (IRB) at each participating institution. The accrual period is 2 years and the follow up period is 3 years. The screening program includes history taking, physical examinations, laboratory tests, chest X-ray, EKG, and so on. If abnormal results requiring treatment were found within the screening, the patient will be given a proper treatment and the enrollment can be cancelled.

**Fig. 1 Fig1:**
[figure not shown]
Flowdiagram of the trial

Arm 1 (conventional chemotherapy group): the patients, who are allocated to the arm 1, will undergo TME at 9 weeks after the CRT. They will receive 8 cycles of adjuvant chemotherapy with mFOLFOX6 (5-fluorouracil with Oxaliplatin) every 2 weeks within 6 weeks after TME. Arm 2 (consolidation chemotherapy group); the patients, who are allocated to the arm 2, will receive 3 cycles of mFOLFOX6 every 2 weeks after neoadjuvant CRT, and undergo TME at 9 weeks after the CRT. Then patients will receive the additional 5 cycles of adjuvant chemotherapy with mFOLFOX6 within 6 weeks after TME.

TME is intended to obtain a complete resection of the tumor (R0) with negative resection margins and adequate lymphadenectomy. The surgeon can decide stoma formation, medial-to-lateral or lateral-to-medial approach, vascular ligation (i.e. high tie or low tie), splenic flexure mobilization as well as the method of operation including open, laparoscopic, or robotic surgery. A complete resection (R0) or microscopic remnant resection (R1) should be confirmed by pathologists after TME. Patient with visible incomplete resection (R2) or distant metastasis is excluded in this study.

mFOLFOX6 regimen is composed of levoleucovorin (200 mg/m^2^) or leucovorin (400 mg/m^2^), oxaliplatin (85 mg/m^2^) for 2 h, then 5-FU (400 mg/m^2^) bolus followed by 5-FU (2400 mg/m^2^) for 46 h. All chemothrapy-related adverse events will be checked every cycle. Patients older than 70 years will receive chemotherapy as 75% reduced dose for the safety. [27–29] When the absolute neutrophil count decreased less than 1500/μl or any drug-related adverse effects of grade 3 were noted, dose reduction or delay of chemotherapy will be considered. However, delay of chemotherapy does not mean delay of TME in Arm 2. Even though a patient in Arm 2 lacks one or two cycles of consolidation chemotherapy due to chemotherapy-related adverse events, the patient will underwent TME at 9 weeks after CRT, and the data will be analyzed as intention-to-treat. All patients will equally visit every 3 months for 2 years, and then every 6 months for 3 years. Physical examination and laboratory test will be performed every 3 months, abdominal-pelvic CT scan every 6 months, chest CT every 1 year, and colonoscopy will be performed at 1 and 5 years to detect metastasis or recurrence.

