### Objective

The authors will compare pCR rates and 3-year disease-free survival (DFS) rates as the primary endpoints between the two groups. pCR is defined no residual tumor or complete replacement of fibrosis in the surgical specimen (i.e. Mandard 1 or Dworak 4). 3-yr DFS is defined as proportion of the patients who survive without any local or distant recurrence/metastasis at the 3 years of follow up.

Secondary endpoints are radiotherapy-related toxicity, R0 resection rate, tumor response rate, surgery-related morbidity, and severity of peripheral neuropathy at 3 years. Acute and chronic toxicity will be recorded in the electronic case report form (eCRF). R0 resection rate is defined as the proportion of R0 resection among all TME specimens according to the pathologic results. TME quality evaluation will be performed by surgeons or pathologists: complete, nearly complete, and incomplete [30]. Tumor response rate is represented as grade of Mandard or Dworak [31, 32]. Postoperative complication within 30 days after TME will be recorded according to the grade of Clavien-Dindo classification of surgical complications [33]. Severity of peripheral neuropathy will be assessed at 3 years as well as every cycles of chemotherapy. The grade of any adverse event will be recorded by Common Terminology Criteria for Adverse Events (CTCAE) 4.0 [34]. Operative, pathologic, and chemotherapeutic reports are documented in the eCRF.

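### Excluding patients with R2 resection (and, as the text most naturally reads, metastasis found at surgery) is a post-randomisation exclusion that removes early DFS failures and conflicts with the endpoint definitions

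*Protocol article*

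**What the plan says.** All places are in the protocol article.

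- **Allocation (Study design).** Patients who have received CRT "will be randomized in a 1:1 ratio into one of the following arms after screening".
- **Between allocation and surgery (Study design, arm descriptions after Fig. 1).** Arm 2 patients "will receive 3 cycles of mFOLFOX6 every 2 weeks after neoadjuvant CRT, and undergo TME at 9 weeks after the CRT". Arm 1 has TME at the same 9 weeks, with no chemotherapy in the interval.
- **Resection status (Study design, TME paragraph).** "A complete resection (R0) or microscopic remnant resection (R1) should be confirmed by pathologists after TME". The next sentence is the rule at issue: "Patient with visible incomplete resection (R2) or distant metastasis is excluded in this study".
- **Intention-to-treat (Study design, mFOLFOX6 paragraph).** For an Arm 2 patient who misses one or two consolidation cycles, "the patient will underwent TME at 9 weeks after CRT, and the data will be analyzed as intention-to-treat". The article makes no other intention-to-treat statement.
- **Endpoints (Objective).** 3-year DFS is the "proportion of the patients who survive without any local or distant recurrence/metastasis at the 3 years of follow up". pCR is judged on the surgical specimen. "R0 resection rate is defined as the proportion of R0 resection among all TME specimens".
- **Entry criteria (Study design).** Distant metastasis and clinical T4 disease are already exclusions at entry.
- **Drop-out.** The list covers unacceptable adverse events, a need for treatment not approved in the trial, refusal and pregnancy. It names neither R2 nor metastasis.

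**The concern.** R2 status cannot be known before TME, and TME comes after allocation. A rule that takes R2 patients out of the study therefore selects on something that happens after randomisation. The arms differ in exactly this window, because one receives three cycles of mFOLFOX6 and the other none, so equal exclusion rates cannot be presumed. The patients removed are early failures on DFS, a primary endpoint. The arm with more of them gains more from their removal.

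The R0 endpoint is affected as well. If R2 cases leave the study, only R1 can count against R0, and the reported R0 rate rises. If such patients also leave follow-up, no later analysis can recover them.

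**Working it through.** **1. The plan's own figures.** These set the number per arm used below.

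- pCR, 15% vs 30%, one-sided 0.025, power 90%, pooled variance: n = [1.960 × √(2 × 0.225 × 0.775) + 1.282 × √(0.15 × 0.85 + 0.30 × 0.70)]² / 0.15² = 160.8, so 161 per arm. 161/0.9 = 178.9, so 179, as stated.
- DFS, 65% vs 80% at 3 years: HR = ln 0.80 / ln 0.65 = 0.518. Schoenfeld events = 4 × (1.960 + 1.282)² / (ln 0.518)² = 97.1, so 98. With exponential survival, 2 years' uniform accrual and 3 further years of follow-up, the mean event probability is 0.346. 98/0.346/2 = 141.7, so 142 per arm, and 142/0.9 = 157.8, so 158, as stated.

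The sample size is sound. The problem is who is analysed.

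**2. The passages side by side.**

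| Item | TME paragraph | Elsewhere in the article |
|---|---|---|
| R2 at TME | out of the study | Objective: R0 rate taken over every TME specimen, so R2 belongs in the denominator |
| Metastasis found at TME | out of the study, on the natural reading | Objective: metastasis counts against DFS |
| Metastasis at entry | – | Study design: already an exclusion criterion |

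**3. Size of the bias.** The documents give no R2 or metastasis rate, so every exclusion rate here is an assumption. Assume also that each excluded patient is a DFS failure, that there are 161 per arm before exclusion, and that 3-year proportions are compared by normal approximation. With true rate p in both arms and excluded fraction e in an arm:

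- observed rate = p/(1 − e), on n = 161(1 − e) patients
- one-sided error = P(Z > 1.960 − difference/SE), where the difference is Arm 2 minus Arm 1

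Worked case, p = 0.70, Arm 1 excludes 4% and Arm 2 excludes 8%:

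- Arm 1: 0.70/0.96 = 72.9% on 154.6 patients. Arm 2: 0.70/0.92 = 76.1% on 148.1 patients.
- Difference 0.0317; SE = √(0.729 × 0.271/154.6 + 0.761 × 0.239/148.1) = 0.0501; ratio 0.633.
- Error = P(Z > 1.327) = 0.092.

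| True DFS, both arms | Excluded, Arm 1 / Arm 2 | Observed DFS, Arm 1 / Arm 2 | Difference (points) | One-sided error |
|---|---|---|---|---|
| 70% | 4% / 8% | 72.9% / 76.1% | +3.2 | 0.092 |
| 70% | 8% / 4% | 76.1% / 72.9% | −3.2 | 0.005 |
| 65% | 2% / 5% | 66.3% / 68.4% | +2.1 | 0.059 |
| 65% | 5% / 2% | 68.4% / 66.3% | −2.1 | 0.009 |
| 65% | 5% / 5% | 68.4% / 68.4% | 0 | 0.025 |

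Under the design alternative:

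- 5% excluded in both arms turns 65/80% into 0.65/0.95 = 68.4% and 0.80/0.95 = 84.2%.
- 5% excluded in Arm 1 and 2% in Arm 2 gives 68.4% and 0.80/0.98 = 81.6%. The planned 15-point difference shrinks to 13.2 points.

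**4. pCR.** Suppose all excluded patients are non-pCR, which is the most that exclusion could do. With a true rate of 15% in both arms and 4% / 8% excluded, the observed rates are 0.15/0.96 = 15.6% and 0.15/0.92 = 16.3%. The difference is 0.7 points and the one-sided error about 0.036.

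**The case against.** **The metastasis half may only restate the entry criterion.** This is possible. Its place directly after pathological confirmation of the resection points to findings at surgery, but the wording does not settle it. The R2 half cannot be read that way.

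**Exclusion may mean leaving protocol treatment, not leaving the analysis.** The Objective section favours that reading, and the Drop-out list's item on unapproved treatment might cover such patients. But the sentence speaks of the study, and nothing in the article says that these patients stay in the analysis. The ambiguity is a reason to reword the sentence.

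**A reader might infer a flat contradiction with intention-to-treat.** The text does not go that far. "and the data will be analyzed as intention-to-treat" closes a sentence about Arm 2 patients with missed cycles and is no general commitment. The two sentences sit badly together; the clash with the Objective section is the firmer point.

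**A reader might infer that the rule favours consolidation.** The documents do not support a direction. Inflation needs more early failures in Arm 2. If earlier chemotherapy prevents them, the rule works against Arm 2 and the test is conservative. Entry is also limited to non-T4, non-metastatic disease, so the rates may be low.

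**A reader might infer that every excluded patient fails on pCR and R0.** That holds for R2. It does not follow for metastasis: both endpoints are judged on the specimen, and a patient with a distant metastasis can still have a pCR, R0 specimen.

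**Conclusion.** The point stands. The R2 exclusion is post-randomisation by necessity, and the metastasis exclusion is so on its most natural reading. Followed as written, the rule removes early DFS failures and cannot be squared with the DFS definition or the R0 denominator. The article states the rule outright, so this is not a detail left to an analysis plan.

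The size is open because no exclusion rates are given. In the unequal cases tabulated, the spurious DFS difference is about 2 to 3 points in either direction, and the nominal 0.025 becomes anything from about 0.005 to 0.092. Equal exclusion leaves the error at 0.025 but raises DFS in both arms above the design values. The effect on pCR is small. These figures rest on assumed rates, on every excluded patient being a DFS failure, and on a comparison of 3-year proportions. Confidence is high for R2 and lower for metastasis, where the reading is less certain.

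**What to change.** Delete the sentence as an exclusion from the study and state instead:

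- All randomised patients are followed and analysed in the arm allocated.
- R2 resection, or distant metastasis first found after randomisation, is a DFS event at the date of detection.
- R2 is non-pCR and stays in the R0 denominator as non-R0.
- Patients with metastasis who undergo TME are classified for pCR and R0 by their specimen, as the Objective section defines.
- Metastasis is an exclusion only when found before randomisation.

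An analysis limited to R0/R1 resections may be shown as a sensitivity analysis. The TME paragraph and the Objective section must be reconciled. The change concerns analysis only, and nothing is proposed on further treatment of these patients.

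The cost is wording, together with continued follow-up of patients who would otherwise have been removed. Operative and pathology reports already go into the eCRF. Reported DFS and R0 rates will be slightly lower than under the exclusion. The total of 358 is unchanged.
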